# GASTRICHIP: D2 resection and hyperthermic intraperitoneal chemotherapy in locally advanced gastric carcinoma: a randomized and multicenter phase III study

**DOI:** 10.1186/1471-2407-14-183

**Published:** 2014-03-14

**Keywords:** Gastric adenocarcinoma, Hyperthermic intraperitoneal chemotherapy, Oxaliplatin, Peritoneal carcinomatosis

## Abstract

**Background:**

In Europe, gastric cancer remains diagnosed at advanced stage (serosal and/or lymph node involvement). Despite curative management combining perioperative systemic chemotherapy and gastrectomy with D1-D2 lymph node dissection, 5-year survival rates of T3 and/or N + patients remain under 30%. More than 50% of recurrences are peritoneal and/or locoregional. The use of adjuvant hyperthermic intraperitoneal chemotherapy that eliminates free cancer cells that can be released into peritoneal cavity during the gastrectomy and prevents peritoneal carcinomatosis recurrences, was extensively evaluated by several randomized trials conducted in Asia. Two meta-analysis reported that adjuvant hyperthermic intraperitoneal chemotherapy significantly reduces the peritoneal recurrences and significantly improves the overall survival. As it was previously done for the evaluation of the extension of lymph node dissection, it seems very important to validate on European or caucasian patients the results observed in trials performed in Asia.

**Methods/design:**

GASTRICHIP is a prospective, open, randomized multicenter phase III clinical study with two arms that aims to evaluate the effects of hyperthermic intraperitoneal chemotherapy with oxaliplatin on patients with gastric cancer involving the serosa and/or lymph node involvement and/or with positive cytology at peritoneal washing, treated with perioperative systemic chemotherapy and D1-D2 curative gastrectomy. Peroperatively, at the end of curative surgery, patients will be randomized after preoperatively written consent has been given for participation. Primary endpoint will be overall survival from the date of surgery to the date of death or to the end of follow-up (5 years). Secondary endpoint will be 3- and 5-year recurrence-free survival, site of recurrence, morbidity, and quality of life. An ancillary study will compare the incidence of positive peritoneal cytology pre- and post-gastrectomy in two arms of the study, and assess its impact on 5-year survival. The number of patients to be randomized was calculated to be 306.

**Trial registration:**

EudraCT number: 2012-005748-12, ClinicalTrials.gov identifier:
NCT01882933.

## Background

Stomach is the fourth most common digestive cancer
[1], the second main cause of death from cancer in the world
[2], and the fifth most common cancer in Europe
[3].

### Surgery

Surgery remains the curative treatment of choice for stomach cancer. It consists of a radical subtotal or total gastrectomy with D1 or D2 lymph node Dissection. A logical and reasonable alternative (expert consensus) is therefore to carry out D1 dissection associated with pedicle dissection (common hepatic artery, left gastric artery and proximal splenic artery). This extension corresponds to D2 dissection for antral cancers. When this type of dissection without splenectomy or pancreactectomy is carried out for a cancer of the body or the upper-third of the stomach it is commonly termed D1.5 dissection. Extending the lymph node dissection remains controversial. Two randomized studies and a meta-analysis have shown no benefit from D2 dissection, although a notable benefit was observed in a sub-group of patients with lymph node metastasis
[4-6]. More recently, two well-designed, single-arm studies
[7,8] showed that a modified form of D2 dissection or D1.5 dissection, without splenectomy or pancreatectomy (which increases post-operative morbidity and mortality) has better results in terms of survival than D1 dissection, with acceptable levels of morbidity and mortality.

### Neoadjuvant, adjuvant and perioperative treatments

Systemic perioperative chemotherapy is recommended for the curative treatment of stomach cancer in Europe since the publication of the MAGIC
[9] and Fédération Française des Centres de Lutte Contre le Cancer (FNCLCC) - Fédération Française de Chirurgie Digestive (FFCD)
[10] trials. These studies included 503 and 224 patients respectively, presenting with a gastric adenocarcinoma or adenocarcinoma of the cardia treated with surgery associated, or not, with two or three preoperative, and three postoperative cycles of systemic chemotherapy (ECF or 5-Fluorouracil (5-FU) cisplatin). The 5-year survival rate was 36% and 38% respectively in the experimental arm, compared to 23% and 24% respectively in the control arm (surgery alone). The postoperative chemotherapy was not always feasible: only 40% of patients followed the postoperative treatment regimen in the MAGIC trial and 50% in the FNCLCC-FFCD trial.

Adjuvant chemo-radiotherapy was shown to be effective in a phase III study by MacDonald et al.
[11] This tested chemotherapy (FUFA: 5-FU/Folinic Acid) prior to, and following chemo-radiotherapy (FUFA + 45 Gy) and demonstrated its efficacy in terms of median survival (36 *vs* 27 months). Two-thirds of the patients include were at stages T3 or T4 and 85% had node positive. The main criticism of this trial is that in 54% of cases lymph node dissection was D0. For many experts, this therefore limits the applicability of adjuvant chemo-radiotherapy following resection. This chemo-radiotherapy can be considered as an alternative for certain patients in good general and nutritional health with lymph node invasion having undergone adequate lymph node Dissection. A retrospective study suggested that replacing FUFA with simplified LV5FU2 (Leucovorin/5-FU) reduces toxicity
[12]. Another non-randomized comparative study assessed postoperative chemo-radiotherapy for patients having undergone D2 dissection of over 85%, and reported a benefit from this adjuvant treatment for stages IIIA, IIIB and IV
[13].

A recent meta-analysis of 17 randomized trials including a total of 3,838 patients reported a benefit in terms of overall survival from using systemic postoperative chemotherapy 5-FU *vs* surgery alone [HR 0.83 (95% CI 0.74-0.94)]
[14].

### Peritoneal recurrence

Stomach cancer has the highest rate of peritoneal recurrence of all digestive cancers. After curative surgery, the main reason for treatment failure is peritoneal recurrence which, according to the literature, occurs in 40 to 60% of cases, despite extensive surgery including D2 lymph node dissection
[15,16].

Several factors favorable to peritoneal recurrence have been identified: invasion of the serosa (T3, T4 tumors)
[17,18], detection of free cancer cells in the peritoneal wash liquid
[19,20], invasion of the lymph nodes
[21], and signet ring cells adenocarcinoma
[22].

### Rationale for hyperthermic intraperitoneal chemotherapy (HIPEC)

The failure rate for curative surgical treatment for patients with stomach cancer is mainly due to peritoneal recurrence. It would therefore seem appropriate to offer preventive treatment to reduce the risk of peritoneal recurrence in at-risk patients and thereby reduce the failure rate. The HIPEC technique is increasingly used in the curative treatment of primary and digestive peritoneal carcinomatosis, in association with cytoreductive surgery
[23-25]. It is recommended for treating pseudomyxoma peritonei and peritoneal mesothelioma
[25,26] and it is currently being assessed in France for use in the curative and preventive treatment of colorectal and ovarian carcinomatosis in several phase III studies funded by the French clinical research projects funding program (PHRC): PRODIGE 7/ACCORD 15/0608 (ClinicalTrials.gov number NCT00769405, ProphyloCHIP (ClinicalTrials.gov number: NCT01226394), CHIPOR (ClinicalTrials.gov number NCT01376752).

Intraperitoneal chemotherapy has the advantage of putting the intraperitoneal tumor tissue (which at the beginning of growth is small or non-vascularized) and free cancer cells into direct contact with high concentrations of cytotoxic agents, limiting the systemic concentrations and thereby the risk of toxicity. The cytotoxic effect of heating to 42.5°C has been demonstrated *in vitro*[27] and it has also been demonstrated that the hyperthermia increases the effectiveness of certain molecules (mitomycin C, cisplatin, oxaliplatin), either by increasing their cytotoxicity, or by increasing their penetration into the tumor tissue
[28,29].

### Results for HIPEC used as a curative and preventive treatment for gastric cancer

For gastric carcinomatosis, the association of complete cytoreductive surgery (CCS) and HIPEC is the only therapeutic strategy to achieve long-term survival. A retrospective study of 159 patients with gastric carcinomatosis treated with CCS and HIPEC, reported a 5-year survival rate of 23%. These extended survival rates was obtained in rigorously selected patients presenting with local, resectable carcinomatosis
[30]. A recent randomized phase III study demonstrated the benefit of HIPEC (cisplatin and mitomycin C) associated with CCS. Median survival was 11 months in the CCS + HIPEC group as compared to 6.5 months in the group receiving CCS alone (p = 0.046)
[31]. The benefit of HIPEC was greater in patients with synchronous carcinomatosis.

Several asian authors have reported a potential benefit from using intraperitoneal chemotherapy with or without hyperthermia, as a complement to curative surgery, in the absence of carcinomatosis
[32-34].

Fujimoto et al.
[35] recruited 141 patients and showed that HIPEC significantly reduced the incidence of peritoneal recurrence (p < 0.001), and increased the survival rate (p = 0.03) with no postoperative adverse events. Yonemura et al.
[36] randomized 139 patients into 3 arms: surgery alone, surgery with HIPEC and intraperitoneal chemotherapy without hyperthermia. The 5-year survival rate was 61% in the HIPEC group as opposed to 43% and 42% in the other two groups. In 2001 Kim and Bae
[37] published the results of a controlled study on 103 patients presenting with a gastric carcinoma with invasion of the serosa, who underwent surgical resection alone or associated with HIPEC. The 5-year survival rate was significantly higher in the experimental group when stage IV patients were excluded (p = 0.0379). The most common types of recurrence were locoregional in the HIPEC group and peritoneal in the control group. Yan et al.
[38] published a meta-analysis which also demonstrated that using HIPEC as an adjuvant treatment significantly improved the survival rates of patients with stomach cancer (HR = 0.60; CI 95% = 0.43 to 0.83; p = 0.002). This meta-analysis suggested that intraperitoneal chemotherapy delivered intraoperatively with hyperthermia was a more effective approach than the delayed regimen. More recently, another meta-analysis also showed the potential benefit of using HIPEC for patients with an advanced gastric cancer in an adjuvant setting
[39]. The benefit of using HIPEC as an adjuvant treatment for advanced gastric cancer has been reported in several randomized studies and a meta-analysis
[38]. However these studies included patients who were almost exclusively of Asian origin. It has been formally demonstrated that Asian and Caucasian gastric cancers differ in terms of epidemiology, diagnosis, treatment and prognosis. On the subject of lymph node dissection for example, several randomized studies in Asia and Japan have validated D2 dissection. In Europe, two randomized studies were carried out to assess the benefit of D2 dissection and the conclusions of these studies differ from the Asian studies
[8,40].

Given that curative treatment failure in Western countries is mainly due to peritoneal recurrence and that a meta-analysis composed almost entirely of Asian studies suggests the benefit of HIPEC as an adjuvant treatment, a European study on a Caucasian population would seem to be warranted.

## Methods/design

### Protocol overview

GASTRICHIP is a prospective, open, randomized multicenter phase III clinical study aimed to evaluate the effects of HIPEC with oxaliplatin on patients with gastric cancer involving the serosa and/or lymph node involvement and/or with positive cytology at peritoneal washing, treated by D1-D2 curative gastrectomy (Figure 
1 – Flow chart study). Patients will be randomly assigned in a 1:1 ratio to: Arm A: curative gastrectomy with D1-D2 lymph node dissection + HIPEC with oxaliplatin versus Arm B: curative gastrectomy with D1-D2 lymph node dissection without HIPEC.

**Figure 1 F1:**
[figure not shown]
GASTRICHIP study flow-chart.

### Measures of outcomes and assessments

#### Primary outcome

Overall survival will be measured from the date of surgery to the date of death or to the end of follow-up (5 years).

### Secondary outcomes

Efficacy (3-year and 5-year recurrence-free survivals) and localization of recurrence, morbidity, and quality of life.

### Main inclusion criteria

Patients 18 < age ≤ 75 years old with Karnofsky index ≥ 70% with histologically evidenced resectable T3 or T4 gastric adenocarcinoma for which a curative gastrectomy is scheduled, with invasion into the serosa and/or lymph node metastasis (determined from data obtained by endoscopic ultrasound and chest, abdomen and pelvis Computed Tomography (CT) scan) and/or positive peritoneal cytology (sampled during the preoperative laparoscopy) and/or perforated gastric adenocarcinoma and/or Siewert III adenocarcinoma of the cardia for which a gastrectomy by exclusive abdominal laparotomy is scheduled
[41].

### Exclusion criteria

The following criteria will exclude patients: prior malignant tumors with detectable signs of recurrence, gastric stump adenocarcinoma, presence of comorbidities, notably serious chronic diseases or organ failure, pregnancy or breastfeeding, contraindication to any drug contained in the chemotherapy regimen, life threatening toxicity before surgery, distant metastases (liver, lung. ovaries, etc.), tumoral infiltration of the head or body of the pancreas, patients presenting an adenocarcinoma of the cardia Siewert I or II, existence of any macroscopic peritoneal implants, patients with clinically significant ascites (> 500 cc) even if cytology is negative for cancer cells, in the absence of other non-malignant causes of ascites.

### Randomization

At the time of gastrectomy, if the patient has given informed, written consent and meets inclusion criteria, he will be peroperatively randomized, using an interactive Web response system. Randomization will be balanced and stratified by investigating center; because of the center’s influence in the most studies that evaluated HIPEC, and by the presence or absence of signet ring cells, based on the findings of the preoperative biopsies because of the recent demonstration of its particular prognosis and its relative chemoresistance.

### Treatments

#### Perioperative treatment

All validated perioperative treatments of gastric cancer will be authorized. For patients receiving neoadjuvant chemotherapy, surgery will be scheduled 2 to 4 weeks after the last course of systemic chemotherapy.

The pre- and the post-surgery chemotherapy regimen administrated to a patient must be the same except in case of toxicity, or progression.

### Pre-therapeutic work-up

Patients eligible for the study will be seen in clinics following the explorative laparoscopy to check the inclusion and exclusion criteria. The patient will be required to give written informed consent to participate to this clinical study before any non routine screening tests or evaluations are conducted. Patients eligible for the study will be seen in clinics following the explorative laparoscopy to check the inclusion and exclusion criteria. The following assessments should be performed: Performance Status, upper intestinal endoscopy, endoscopic ultrasound, Thoraco-Abdomino-Pelvic CT scan, PET Scan (optional), laboratory exams: serum CEA, CA19.9 and CA72.4 (optional); hemoglobin, leukocytes, neutrophils, platelets, glycemia, AST, ALT, LDH, total bilirubin, alkalin phosphatase, serum albumin, total protein, plasmatic APTT, PT and INR; creatinine clearance and serum creatinine. Staging videolaparoscopy of the abdominal cavity and peritoneal cytology testing will be carried out following the same procedure as during gastrectomy. Patients with macroscopic peritoneal carcinomatosis not visible during the preoperative morphological examinations will be excluded from the study.

### Preoperative work-up

Patients should be re-evaluated within 21 days before surgical procedure. The following assessments should be performed: Performance Status, Thoraco-Abdomino-Pelvic CT scan, PET Scan (optional), laboratory exams: serum CEA, CA19.9 and CA72.4 (optional); hemoglobin, leukocytes, neutrophils, platelets, glycemia, AST, ALT, LDH, total bilirubin, alkalin phosphatase, serum albumin, total protein, plasmatic APTT, PT and INR; creatinine clearance and serum creatinine, quality of life assessment (QLQ-C30 and QLQ-STO 22).

Patients with evidence of metastatic disease will be excluded from study.

### Surgical technique

At the opening of the abdomen, surgical exploration will be performed in order to compare data collected at preoperative videolaparoscopy with current operative findings including the effects coming from preoperative chemotherapy, namely the downstaging as far as T parameter is concerned, presence of serosal involvement and its extent, the absence of distant metastases and the feasibility of a D1-D2 resection with curative intent.

Peritoneal washing will then be performed: the abdomen will be irrigated with 200 ml of 0.9% NaCl solution (normal saline), left in the peritoneal cavity for 2 minutes and then all fluid will be aspirated from the four abdominopelvic quadrants [Left Upper Quadrant (LUQ) - Right Upper Quadrant (RUQ) - Left Lower Quadrant (LLQ) - Right Lower Quadrant (RLQ)]. All the collected fluid will be sent to the corresponding lab, where specimens for regular cytological analysis, cell blocks and immunohistochemistry (ancillary cytological study) will be sent to the Centre de Biologie et de Pathologie Est – Hospices Civils de Lyon.

All the patients will undergo a D1-D2 gastrectomy, carried out according to Japanese guidelines and to the European recommendations for the preservation of spleen and pancreas
[42]: lymphadenectomy will consist of removal of nodal groups 2 to 9 as specified by the JGCRS; group 1 will be added when total gastrectomy is performed and group 12 in distal cancers. *Ex vivo* separation of lymph node groups in individual containers before the surgical specimen is submitted to the pathologist is recommended. At the end of the gastrectomy procedure the peritoneal washing will be repeated with the same procedure.

Following randomization, the patients treated into the experimental Arm receive intravenous 5-FU 400 mg/m^2^ + calcium levofolinate 10 mg/m^2^) as systemic chemotherapy induction for HIPEC 15 min before HIPEC started. At the end of the procedure the patients in the experimental Arm will undergo HIPEC.

### HIPEC techniques

The HIPEC can be carried out by open or closed abdomen technique. With the Open abdomen technique, after the D2 resection is complete, the inflow catheter is positioned in the gastric resection bed. Drains are placed through separate stab wounds in the abdominal flanks and positioned between the liver and undersurface of the right hemidiaphragm behind the spleen and in the pelvis. Number of drains used is left to the surgeon’s discretion and according to the specifications of the HIPEC circuit used. One of the two temperature probes will be secured near the tip of the inflow catheter and the other in the pelvis. Using a monofilament running suture, the skin edges are secured to the Thompson self retaining retractor, and a plastic sheath is incorporated into these sutures to create an open space beneath. A slit in the plastic cover is made to allow the surgeon hand access to abdomen and pelvis. During the perfusion all the anatomic structures within the abdominal cavity are uniformly exposed to heat and to chemotherapy. A roller pump forces the chemotherapy solution (oxaliplatin 250 mg/m^2^ with 2 Liters of G5%/m^2^) into the abdomen through the inflow catheter and pulls it out through the drains. A heat exchanger keeps the intraperitoneal fluid at 42°-43°C. After the intraoperative perfusion is complete (30 minutes), the abdomen is closed and the drains are left in place in the postoperative period until the discharge from the peritoneal cavity subsides. With the Closed abdomen technique, surgery is completed with anastomosis and drains positioning as in the Open technique, the abdominal wall sutured. External manual shaking of the abdomen will be carried out for optimization of chemotherapy distribution. The anastomoses will be constructed either before or after HIPEC administration.

### Follow-up

After HIPEC, patients will remain in the Intensive Care Unit as long as required (it will be remained at the perioperative team’s discretion, depending on patient’s needs and postoperative clinical progress). They will be evaluated with clinical examination daily. Each day for the first week and each third day thereafter, laboratory exams will be performed in order to assess haematological, renal and hepatic function. Locoregional toxicity and systemic toxicity will be evaluated according to the Common Terminology Criteria for Adverse Events (CTC-AE V4.0) from the National Cancer Institute.

Once an early postoperative follow-up four weeks after gastrectomy, the visits of follow-up are based on the date of the surgery every 3 months for the first 2 years following surgical procedure and twice a year for the last 3 years. For all patients clinical follow-up with all events and endpoints will be collected and analyzed during 5 years from their inclusion (except for patients died, lost of follow-up or expressed their refusal).

### Criteria for premature discontinuation of the patient’s study participation

Patients can be withdrawn from the study under the following circumstances: death, disease progression, initiation of alternate anti-neoplastic therapy, toxicity, intercurrent illness, non compliance (including loss of patient to follow-up), voluntary withdrawal, failure to meet the eligibility criteria.

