### Sample size calculation and statistical considerations

This study is designed as a randomized phase III in order to compare the 5-year overall survival in patients with advanced gastric carcinoma randomized to hyperthermic intraperitoneal chemotherapy administration versus that of patients randomized to control arm.

The hypotheses are the following: 5-year overall survival in the control group of about 30%
[9,10]; 5-year overall survival in the intervention group of about 45% (i.e. an HR of 0.67)
[45]; a maximum follow-up time of 5 years; an alpha of 5%, two-sided. With this hypothesis and to have a 80% power, a total of 306 patients will have to be randomized. Since 5% of patients are expected to excluded during surgery (peritoneal carcinomatosis), a total of 322 patients will be included.

The effectiveness analysis will be carried out on the intention-to-treat population, defined as all patients included. A second analysis will be conducted on the “treated” population, determined according to the treatment actually administered (*per protocol* analysis). Overall survival will be measured from the date of surgery up to the date of death, regardless of the cause, or to the end of follow-up (5 years). The Kaplan-Meier method will be used to estimate the survival curves. Median survival will also be given and differences between the two groups assessed using a logrank test. This analysis will then be confirmed using a Cox regression analysis taking into account the center effect (frailty Cox model). The conditions for using the Cox regression analysis will be checked.

An intermediate analysis of toxicity will be realized at least every six months or every 50 patients randomized from the start of patients’ recruitment. The number of SAEs and AEs of severe (grade III-IV) with their accountability will be described.

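### The withdrawal list and the 5-year follow-up rule contradict each other, so deaths after progression could go uncounted where sites act on the list after randomisation

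*Protocol article*

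**What the plan says.** Three parts of the protocol article bear on this.

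- **Criteria for premature discontinuation of the patient's study participation.** The rule given there is: "Patients can be withdrawn from the study under the following circumstances: death, disease progression, initiation of alternate anti-neoplastic therapy, toxicity". The sentence continues with intercurrent illness and non-compliance (under which it places loss to follow-up), and ends with "voluntary withdrawal, failure to meet the eligibility criteria". Heading and sentence both speak of the study. Neither separates stopping a treatment from stopping follow-up, and neither distinguishes the time before randomisation from the time after it.
- **Follow-up.** "For all patients clinical follow-up with all events and endpoints will be collected and analyzed during 5 years from their inclusion". The exceptions stand in brackets: "except for patients died, lost of follow-up or expressed their refusal".
- **Sample size calculation and statistical considerations.** The primary endpoint counts every death: "Overall survival will be measured from the date of surgery up to the date of death, regardless of the cause", with 5 years as the limit. On the population: "The effectiveness analysis will be carried out on the intention-to-treat population, defined as all patients included". The design compares 5-year survival of 30% with 45% at 80% power and two-sided 5% alpha, in 306 randomised patients. The only inflation, to 322, covers exclusions during surgery.

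**The concern.** For several kinds of patient the two sections give opposite instructions. One allows the patient to leave the study; the other requires that patient's events to be collected for 5 years.

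Progression matters most. The Background names peritoneal recurrence as the main reason for failure after curative surgery, so a patient who has just progressed is at high risk of the primary event. If a site ended participation then, the patient would be censored shortly before a likely death. Kaplan-Meier and logrank methods assume that censored patients carry the same future risk as those still followed, which would be false here. Because HIPEC is intended to change the frequency and site of recurrence, the censoring could also differ between arms.

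Nor does the timing of the randomised treatment explain the list. HIPEC is a single 30-minute perfusion during surgery, so a later progression leaves no randomised treatment to stop.

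Three things are at stake: survival estimates that read too high, fewer deaths than the design needs, and a comparison that may be distorted.

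**Working it through.** **1. The two rules side by side**

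| Circumstance | Permitted ground for leaving the study | Exception to 5-year collection |
|---|---|---|
| Death | yes | yes |
| Loss to follow-up | yes (under non-compliance) | yes |
| Refusal / voluntary withdrawal | yes | yes |
| Disease progression | yes | no |
| Alternate anti-neoplastic therapy | yes | no |
| Toxicity | yes | no |
| Intercurrent illness | yes | no |
| Other non-compliance | yes | no |
| Failed eligibility | yes | no |

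The first three rows agree; the last six conflict.

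**2. The plan's own figure**

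Inputs from the sample size section: 5-year survival 30% and 45%, two-sided alpha 5%, power 80%, 5 years of follow-up. Allocation is 1:1 (Protocol overview).

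- HR = ln 0.45 / ln 0.30 = 0.663 (the article gives 0.67).
- Mean 5-year death probability = (0.70 + 0.55)/2 = 0.625.
- Freedman: (1.960 + 0.842)² × ((1 + 0.663)/(1 − 0.663))² gives 192 deaths, and 192/0.625 = 307.2 patients.
- Schoenfeld: 187 deaths and 299.2 patients at HR 0.663; 196 deaths and 313.6 patients at HR 0.67.

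All three totals are within 3% of 306, so the figure reproduces. It implies 306 × 0.625 = 191 deaths, which assumes complete 5-year survival follow-up. Schoenfeld power with 191.25 deaths is Φ(|ln 0.663| × √191.25 / 2 − 1.960) = 81.0% (79.1% at HR 0.67).

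**3. Deaths lost at random**

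The documents give no withdrawal rate, so the share lost is an assumed range. Same power formula, with D = 191.25 × (1 − share lost):

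| Share of deaths uncounted | Deaths | Power, HR 0.663 | Power, HR 0.67 |
|---|---|---|---|
| 5% | 181.7 | 79.0% | 77.0% |
| 10% | 172.1 | 76.8% | 74.8% |
| 20% | 153.0 | 71.9% | 69.7% |
| 30% | 133.9 | 66.1% | 63.9% |
| 50% | 95.6 | 51.9% | 49.9% |

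This shows the loss of events only, not bias.

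**4. Withdrawal at progression**

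In an illness-death simulation, patients progress and then die, or die without recurrence. Assumptions, none from the documents: death without recurrence 0.02 per year; death after progression 1.0 per year (mean 1 year); treatment effect on progression only; the same withdrawal probability in both arms. Progression hazards of 0.289 (control) and 0.179 (HIPEC) per year were set so that true 5-year survival matches the plan's 30% and 45%. There were 153 patients per arm and 4,000 runs; power is the share of runs with a logrank result favouring HIPEC beyond 1.96.

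| Withdrawn at progression | Deaths observed | Power | 5-year KM, control | 5-year KM, HIPEC |
|---|---|---|---|---|
| 0% | 191 | 81% | 30% | 45% |
| 10% | 174 | 77% | 33% | 48% |
| 25% | 148 | 70% | 38% | 52% |
| 50% | 104 | 57% | 48% | 62% |

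With equal withdrawal, both curves rise and the gap between them changes little: about 15 points at 0%, 10% and 25%, and 13.5 at 50% (61.9 − 48.4). The harm shown is therefore inflated survival and lost power. Withdrawal that differs by arm was not simulated; it could bias the comparison itself.

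**The case against.** The strongest reply is that the article already states the governing rule. The Follow-up section deals directly with endpoint collection, covers all patients and names only three exceptions. The statistical section counts death from any cause and analyses by intention to treat. The discontinuation sentence is only permissive, is condensed enough to list death itself, and never mentions censoring or the end of vital-status collection. This stands: a reader might infer that the protocol orders deaths after progression to be censored, and the text does not say so.

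Timing is the second reply. Patients are included before surgery and randomised during it, with 322 included for 306 randomised. The Preoperative work-up section excludes patients found to have metastatic disease. Progression, toxicity or failed eligibility may therefore describe exits before randomisation. A reader might also infer that ineligible patients are to be removed after randomisation, against intention to treat; the text does not say that either. But the list is not limited to the earlier period, so the possibility stays open.

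Third, the Perioperative treatment section governs systemic chemotherapy and names toxicity and progression as reasons for changing the regimen. Those grounds may thus have been meant for treatment. That is plausible, but the heading and sentence refer to the study.

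Finally, an article may leave off-study procedures to the full protocol. That would excuse silence. It does not excuse two stated rules that disagree.

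**Conclusion.** The contradiction is real and concerns the primary endpoint. Whether any deaths are lost depends on which section sites follow; the documents do not show that any would be. The supportable conclusion is conditional: where a site applies the withdrawal list after randomisation, deaths after progression can go uncounted, and that censoring is informative and possibly arm-dependent.

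Under the stated assumptions, withdrawing 10% to 50% of patients at progression takes power from about 81% to between 77% and 57%, and raises apparent control survival from 30% to between 33% and 48%. The withdrawal rates, the hazards and the restriction of the effect to progression are illustrative. Withdrawing every progressing patient would leave about 18 deaths and 3% power, because only deaths without recurrence would remain and the model gives HIPEC no effect on those. That is a limit of the model, not a forecast, and it is not credible beside the Follow-up rule.

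**What to change.** Reconcile the two sections in one paragraph:

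- For randomised patients, only death, loss to follow-up or refusal of further follow-up ends follow-up. Progression, alternate anti-neoplastic therapy, toxicity, intercurrent illness, other non-compliance and later-discovered ineligibility do not.
- Collect vital status and recurrence for every randomised patient to 5 years.
- Analyse each randomised patient in the arm assigned, including any later found ineligible.
- Limit withdrawal for failed eligibility to patients not yet randomised.

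This concerns data collection and analysis only and leaves treatment decisions untouched. The cost is a wording change and a note to sites. Sample size and the existing 5-year visit schedule stay as they are: with complete follow-up, the 306 patients give about 191 deaths and the planned power. It should be settled while patients are still in follow-up, since survival data missed at a site may be hard to recover later.
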